### Recruitment

The study aims to recruit 60 young people and their families (30 per arm). This is based on guidance from the National Institute for Health Research that a sample size required for a fRCT ranges from 24 to 50 participants [51–54] and other guidance that a sample size as large as 70 may be required [55]. The recruitment site is a research active service. To achieve adequate enrolment in the trial a member of the research team will regularly attend team meetings to answer any questions about the study and identify potential participants.

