##### Expressed emotion

Level of expressed emotion will be measured using three instruments; one adolescent and two parent-focused. Adolescents will complete the Brief Dyadic Scale of Expressed Emotion (BDSEE) [71], which includes three subscales; criticism, emotional overinvolvement and warmth. The BDSEE has been shown to have good reliability and validity in adolescent and eating disorder populations [71, 72]. Parent’s own perceived level of criticism and overinvolvement will be assessed using the self-report Family Questionnaire (FQ) [73], a valid measure of expressed emotion [73] Parents also complete the verbal Five Minute Speech Sample (FMSS) [74] task. This requires each parent/carer to talk about their thoughts and feelings about the patient for five uninterrupted minutes. This speech is recorded and later coded for overall level of expressed emotion. This is considered a valid measure of expressed emotion [75]. The FMSS will be used to identify EE categories (high/low criticism, high/low emotional overinvolvement, positive/negative relationship). Level of criticism and emotional overinvolvement (continuous variables) will be derived from the BDSEE and FQ for young people and parents, respectively.

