### Analysis plan

Primary outcomes (feasibility and acceptability) will be reported using means, standard deviations and ranges, or medians and interquartile ranges of the primary outcomes listed above (see Table 1). Numeric feasibility and acceptability parameters (recruitment rate, missing data, loss to follow-up, treatment dropout) will be categorised as either green (> 75% response rate), amber (50–75% response rate), or red (< 50% response rate). Numeric values will also be considered in the context of non-numeric/free-response data where available. Parameters in the red and amber zone will be carefully considered and/or amended for the design of the main trial.

Linear mixed models [78] will be used to explore any changes in secondary outcomes (young person and parent factors) over the treatment and follow-up period. These models are commonly used statistical methods to analyse longitudinal data [79]. Simulation studies have shown them to be robust with moderate sample sizes, as in this study, when the data are normally distributed or lightly skewed [80–82]. This approach allows for random factors (both between and within-subject variability) to be included, meaning individual differences at baseline (e.g., demographic and illness characteristics) can be taken into account, as well as the possibility of individual differences in change trajectories during treatment.

Change in weight will also be calculated for the subgroup who are underweight at baseline (< 90%mBMI) or for whom weight gain is an identified treatment target. Baseline characteristics (gender, illness severity and duration, prior treatment, intact family status) and post-treatment characteristics (additional treatment type and dose, re-referral to services, referral to higher levels of care) will also be reported and groups compared using exploratory t-tests. Group differences between those with available data and those with missing data will also be reported and compared using exploratory t-tests. Together, this will be used to identify variables to be considered as strata for randomisation in the larger trial.

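### The t-tests meant to suggest strata for the larger trial do not measure prognostic value, and some of the variables tested cannot be strata

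*Protocol article*

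**What the plan says.** The third paragraph of the protocol article's Analysis plan sets out two sets of comparisons and one use for them.

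- **First comparison.** It covers "Baseline characteristics (gender, illness severity and duration, prior treatment, intact family status" and also "post-treatment characteristics (additional treatment type and dose, re-referral to services, referral to higher levels of care". These "will also be reported and groups compared using exploratory t-tests". The groups are not named.
- **Second comparison.** "Group differences between those with available data and those with missing data will also be reported and compared using exploratory t-tests".
- **Use.** "Together, this will be used to identify variables to be considered as strata for randomisation in the larger trial".

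Two other places matter. Under Recruitment, "The study aims to recruit 60 young people and their families (30 per arm". Under Randomization, allocation is by computer-generated blocks of random size, and no patient characteristic enters the process. The article does not say anywhere that candidate strata will be judged by their relation to outcome.

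**The concern.** A stratification factor is useful if it is known before allocation and predicts the outcome. The Analysis plan names a method and a purpose, and the method does not address either condition.

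- **Baseline variables.** In a randomised trial, a between-arm baseline difference reflects how the allocation happened to fall. The test result carries no information on prognosis.
- **Post-treatment variables.** Additional treatment, re-referral and referral to higher levels of care arise after allocation. A difference between arms may be an effect of treatment, and the variable is not available to stratify on.
- **Available versus missing data.** This contrast is not randomised, so a difference need not be chance. It can show what goes with attrition, but that is not prognosis for outcome.
- **Fit of the test.** Several listed variables are categorical or look so (gender, intact family status, prior treatment, the referrals), and treatment type is nominal. A t-test suits these poorly and has no meaning for a nominal variable.

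At stake is the candidate list handed to the full-size trial. A variable with no prognostic value may enter it because the arms happened to differ, and a strongly prognostic one may be left out because they happened to balance.

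**Working it through.** The article gives no alpha, threshold or power for this step, so there is no stated figure to reproduce. What follows is an illustration under an assumed two-sided alpha of 0.05.

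**Inputs from the protocol article**
- 30 per arm, 60 in total (Recruitment).
- Allocation independent of baseline variables (Randomization).
- Five baseline variables, counting severity and duration separately: gender, illness severity, illness duration, prior treatment, intact family status (Analysis plan).

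**Step 1. Does the between-arm test respond to prognostic strength?** 20,000 trials were simulated with 30 per arm. The baseline covariate x is standard normal. The outcome is y = ρx + √(1 − ρ²)e, with e standard normal and no treatment effect. Two tests were applied at 0.05: the between-arm t-test on x, and the test of correlation between x and y in all 60.

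| Correlation ρ with outcome | Flagged by between-arm t-test | Flagged by association with outcome |
|---|---|---|
| 0 | 4.7% | 4.8% |
| 0.3 | 5.1% | 65.0% |
| 0.5 | 4.8% | 98.7% |
| 0.7 | 5.0% | 100% |

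The between-arm test stays at alpha in every row. The association test rises with ρ. The relevant information is therefore in the data this trial will collect, and the planned comparison does not use it.

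**Step 2. Chance of at least one spurious baseline flag.** With five independent tests: 1 − 0.95⁵ = 1 − 0.774 = 0.226, about 23%.

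**Step 3. Post-treatment variables.** Suppose, as an assumption, that re-referral is 40% in one arm and 20% in the other because of treatment. With 30 per arm this is flagged about 39% of the time. Such a flag reflects a treatment effect and does not yield a stratum.

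**Step 4. Available versus missing.** For an assumed standardised difference of 0.5, power is about 21% with 6 of 60 missing, 34% with 12 and 39% with 15. Even for predictors of attrition, the comparison will often miss a moderate difference.

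**Step 5. Precision of the alternative.** For an observed correlation of 0.3 with all 60 contributing, Fisher's z is 0.310 with standard error 1/√57 = 0.132. The interval on the z scale is 0.310 ± 1.96 × 0.132, or 0.05 to 0.57. Transformed back, the 95% confidence interval for the correlation is about 0.05 to 0.51. This is wide and would be wider after loss to follow-up, but it measures the right quantity.

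**The case against.** The strongest defence is that the plan commits to little. The tests are called exploratory, no threshold is given, the result is a list of candidates, and the Discussion calls all conclusions tentative. The larger trial will need its own protocol, where strata can be justified afresh. The mixed models described in the same section can also take baseline characteristics into account. These points lower the stakes, but a tentative inference from a test that carries no relevant information is still uninformative, and the article does not connect the mixed models to the choice of strata.

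The groups are not explicitly the randomised arms. That is an inference, though a natural one, because the missing-data contrast has its own sentence immediately afterwards.

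The objection to t-tests on categorical data is partly met. With about 30 per arm, a t-test on a 0/1 variable approximates a comparison of two proportions. It is inelegant but not invalid; only the nominal treatment type clearly does not fit.

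A reader might infer more than the text supports in four ways:
- **That strata will be fixed by these tests.** The text only nominates candidates.
- **That chance imbalance accounts for the whole procedure.** The available-versus-missing contrast also feeds it and is not a test of chance imbalance.
- **That the 23% can be raised by counting the post-treatment variables as further tests.** Those may truly differ through treatment, so the calculation under no difference does not apply to them.
- **That linear mixed models will be fitted to the binary categories of the Five Minute Speech Sample.** The Expressed emotion section uses that task to form categories and takes continuous scores from two other instruments. The Analysis plan assigns no model to the categories by name.

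**Conclusion.** The point stands as a mismatch between the stated method and the stated purpose. Because allocation ignores baseline characteristics, between-arm baseline tests flag a variable at the alpha level (about 5% at an assumed 0.05) whatever its prognostic strength. The figure of about 23% for at least one spurious flag rests on that alpha, on independence of the five tests, and on treating significance as the trigger for candidacy; the article states none of these. The 5% applies to the between-arm baseline tests only, not to the whole procedure. The exclusion of post-treatment variables from stratification needs no assumption.

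The consequence falls on the design of the later trial. Randomisation, the primary feasibility and acceptability outcomes and the traffic-light categories in this trial are untouched. The change is still worth making, because informing the full-size trial is this study's declared purpose and the correction is cheap.

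**What to change.** Revise the third paragraph of the Analysis plan as follows.

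1. Describe baseline characteristics by randomised arm, without significance tests.
2. Draw candidate strata only from variables known at randomisation. Judge each by its association with the six-month outcome (for example %mBMI and EDE-A), in both arms pooled and adjusted for arm. Report estimates with 95% confidence intervals, and weigh them alongside published prognostic evidence.
3. Report additional treatment, re-referral and referral to higher levels of care as outcomes only, and take them out of the strata decision.
4. Use the available-versus-missing comparison to plan the handling of missing data in the larger trial.
5. Summarise categorical variables as counts and proportions, with risk differences and confidence intervals for the post-treatment ones, in place of t-tests.

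The cost is a change of wording and one extra regression table from data already being collected. Estimates from 60 participants will be imprecise and should be presented as such.

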### Oversight and monitoring

Trial-related monitoring, audit and reviews may be conducted by the sponsor and research ethics committee at any time, who may request and access source data and other documents. The sponsor or chief investigator may prematurely discontinue the trial at any time. No adverse events are anticipated given the widespread use of both FT-AN and MFT internationally. If indicated, additional treatment can be offered once participants have completed the trial. Trial updates will be regularly provided to the service research steering committee. A data monitoring committee has not been established due to the small size of this trial.

## Discussion

This trial will determine whether it is feasible and acceptable to add a five-day multi-family therapy group to the critical early stages of family therapy for anorexia nervosa. This will inform the design of a full-size RCT to test whether the addition of brief-early MFT to FT-AN improves treatment outcomes for adolescents with anorexia nervosa.

This trial has several strengths. The use of a randomised controlled design will add rigour to the existing MFT evidence base as only one outpatient controlled trial has currently been reported on to date [38]. Additionally, it is the first MFT study to include data collection points during as well as at the end of treatment. This will help explore potential patterns of change during MFT and FT-AN treatment. Similarly, the inclusion of follow-up data collection points also has the potential to help advance the field by increasing our understanding of the process of change during and after both treatments. Lastly, the trial design allows for exploration of effect size changes of some of the key mediators and moderators of treatment outcome [9], which will extend future understanding of potential MFT treatment mechanisms. This will ensure the full-size RCT will be better equipped to be assessing the most suitable variables and in the most acceptable and feasible manner, with the greatest likelihood of being as effective as possible.

Another strength is that the current trial is investigating and testing more efficient, briefer MFT treatment. The five-day MFT model is less resource intensive and likely more manageable for services to offer than the current manualised 10-day model. If it is assessed as feasible and can be rigorously tested in a larger RCT it has the potential to be more broadly integrated within services and may emerge as a new, accessible intensive treatment option.

Despite these strengths all conclusions drawn from this trial will be tentative given the small sample size and number of measures included. Another limitation is that there is only one recruitment site, meaning site specific factors cannot be determined. Another potential limitation is that MFT is added within the first two months of treatment, rather than the first month. Increasingly, data indicates early change within the first month specifically impacts end of treatment outcomes [11, 12], suggesting intensive MFT may be more effective the earlier it is delivered. Due to service constraints and referral rates, having MFT within the first month is unfeasible.

### Trial status

The trial was registered on ISRCTN registry; ISRCTN93437752, on 27 January 2021. Ethics approval was granted for this project in August 2020 by the Stanmore Research Ethics Committee London (IRAS: 234354; REC: 20/LO/0839). Trial recruitment is currently suspended due to the novel coronavirus (COVID-19) pandemic. Recruitment will commence once group-based work is approved by local authorities.

## Data Availability

Data will be made available upon request for those participants who have consented to this.

## Abbreviations

%mBMI: Percentage of median body mass index
BDSEE: Brief dyadic scale of expressed emotion
BEAM: Brief, early adolescent multi-family
COVID-19: Novel coronavirus 2019
DERS: Difficulties in emotion regulation scale
EIST: Expectation of improvement and suitability of treatment
FMSS: Five minute speech sample
FQ: Family questionnaire
fRCT: Feasibility randomized controlled trial
FT-AN: Family therapy for anorexia nervosa
HADS: Hospital anxiety and depression scale
IRAS: Integrated research application system
ISRCTN: International Standard Randomised Controlled Trial Number
MFT: Multi-family therapy
NICE: National Institute for Health and Care Excellence, UK
PIS: Participant information statement
PPI: Patient and public involvement
RCADS: Revised children’s anxiety and depression scale
RCT: Randomized controlled trial
RFQ: Reflective function questionnaire
SOFTA: System for observing family therapy alliances
SOFTA-o: System for observing family therapy alliances observational tool
SOFTA-s: System for observing family therapy alliances self report tool
SPIRIT: The standard protocol items: recommendations for interventional trials
WSAS-Y: Work and social adjustment scale for youth
